**Proposed Sample Size:**  
Sub-group (Name of subgroup e.g. Men, Women) and Number

| Name                                                           | Number | Name                                                           | Number      |
|----------------------------------------------------------------|--------|----------------------------------------------------------------|-------------|
| Survey                                                  |        | Qualitative data collection                             |             |
| Married adolescent girls aged 15-19 years, living with husband | 1120   | Married adolescent girls aged 15-19 years, living with husband | 16          |
| Husbands of married adolescent girls                           | 1120   | Husbands of married adolescent girls                           | 16          |
| Community members aged 35-59 years                             | 576    | Key informants                                                 | 6           |
|                                                                |        | FGD participants                                               | 64          |
|                                                                |        | Total (including quantitative and qualitative)          | 2918 |

**Determination of Risk: Does the Research Involve** (Check all that apply)

|                                                                                                                                                                                                                                                                          |                                                                                                                                                                                                                                                                                                                                                                                                    |
|--------------------------------------------------------------------------------------------------------------------------------------------------------------------------------------------------------------------------------------------------------------------------|----------------------------------------------------------------------------------------------------------------------------------------------------------------------------------------------------------------------------------------------------------------------------------------------------------------------------------------------------------------------------------------------------|
|  Human exposure to radioactive agents?
 Foetal tissue or abortus?
 Investigational new device?
Specify: _____
 Existing data available from Co-investigator? |  Human exposure to infectious agents?
 Investigational new drug?
 Existing data available via public archives/sources?
 Pathological or diagnostic clinical specimen only?
 Observation of public behaviour?
 New treatment regime? |
|--------------------------------------------------------------------------------------------------------------------------------------------------------------------------------------------------------------------------------------------------------------------------|----------------------------------------------------------------------------------------------------------------------------------------------------------------------------------------------------------------------------------------------------------------------------------------------------------------------------------------------------------------------------------------------------|

|                                                                                                                                                                                    |                                     |                          |
|------------------------------------------------------------------------------------------------------------------------------------------------------------------------------------|-------------------------------------|--------------------------|
| Will the information be recorded in such a manner that study participants can be identified from the information directly or through identifiers linked to the study participants? | Yes                                 | No                       |
|                                                                                                                                                                                    |  |  |
| Does the research deal with sensitive aspects of the study participants' sexual behaviour, alcohol use or illegal conduct such as drug use?                                        | Yes                                 | No                       |
|                                                                                                                                                                                    |  |  |

**Could information on study participants, if available to people outside of the research team:**

|                                                                                                                        |                          |                                     |
|------------------------------------------------------------------------------------------------------------------------|--------------------------|-------------------------------------|
| a) Place them at risk of criminal or civil liability?                                                                  | Yes                      | No                                  |
|                                                                                                                        |  |  |
| b) Damage their financial standing, reputation or employability, or social rejection, or lead to stigma, divorce etc.? | Yes                      | No                                  |
|                                                                                                                        |  |  |

**Do you consider this research:** (check one)

☒ Greater than minimal risk      ☐ No more than minimal risk      ☐ Only part of the diagnostic test

**Note: Minimal Risk:** The probability and the magnitude of the anticipated harm or discomfort to participants is not greater than those ordinarily encountered in daily life or during the performance of routine physical, psychological examinations or tests, e.g. the risk of drawing a small amount of blood from a healthy individual for research purposes is no greater than when the same is performed for routine management of patients.

**Risk Group of Infectious Agent and Use of Recombinant DNA**

a) Will specimens containing infectious agent be collected?      ☐ Yes      ☐ No      ☒ Not applicable

b) Will the study involve amplification by culture of infectious agents?      ☐ Yes      ☐ No      ☒ Not applicable

c) If response to questions (a) and/or (b) is 'yes', to which Risk Group (RG) does the agent(s) belong? (Please visit [http://shetu.icddr.org/index.php?option=com\\_content&view=article&id=265&Itemid=677](http://shetu.icddr.org/index.php?option=com_content&view=article&id=265&Itemid=677) to review list of microorganism by Risk Group)

☐ RG1      ☐ RG2      ☐ RG3      ☐ RG4

d) Does the study involve experiments with recombinant DNA?      ☐ Yes      ☐ No      ☒ Not applicable

**Does the study involve any biohazards materials/agents or microorganisms of risk group 2, 3, or 4 (GR2, GR-3 or GR4)?**

☐ Yes      ☒ No

[If the response is 'yes'] I, (print name of the PI) affirm that we will use the standard icddr,b laboratory procedures for biosafety of the hazardous materials/agents or microorganisms in the conduction of the study.

| Sharing with international agencies                | 
No            | 
Yes |                                        |
| Sharing with donors                                | 
No            | 
Yes |                                        |
| Policy brief                                       | 
No            | 
Yes |                                        |
| Other                                              |                                           |                                            |                                        |
| Other                                              |                                           |                                            |                                        |

**Funding:**

|                                                        |                                                                 |                             |
|--------------------------------------------------------|-----------------------------------------------------------------|-----------------------------|
| Is the protocol fully funded?                          |  Yes                         |  No |
| If the answer is yes, please provide sponsor(s)'s name | 1. Department of Foreign Affairs, Trade and Development (DFATD) |                             |
|                                                        | 2.                                                              |                             |
| Is the protocol partially funded?                      |  Yes                                    |  No |
| If the answer is yes, please provide sponsor(s)'s name | 1.                                                              |                             |
|                                                        | 2.                                                              |                             |

**If fund has not been identified:**

|                                              |                              |                             |
|----------------------------------------------|------------------------------|-----------------------------|
| Is the proposal being submitted for funding? |  Yes |  No |
| If yes, name of the funding agency           | 1.                           |                             |
|                                              | 2.                           |                             |

**Conflict of interest:**

Do any of the participating investigators and/or member(s) of their immediate families have an equity relationship (e.g. stockholder) with the sponsor of the project or manufacturer and/or owner of the test product or device to be studied or serve as a consultant to any of the above?

☒ No ☐ Yes (please submit a written statement of disclosure to the Executive Director, icddr,b)

**Proposed Budget:****Dates of Proposed Period of Support Period (\$)**

(Day, Month, Year - DD/MM/YY)

Beginning Date : 01 January, 2023

End Date : 31 March, 2025

**Cost Required for the Budget**

| Years  | Direct Cost | Indirect Cost | Total Cost |
|---------------|--------------------|----------------------|-------------------|
| Year-1 | 163,034            | 23,444               | 186,479           |
| Year-2 | 159,031            | 22,869               | 181,899           |
| Year-3 |                    |                      |                   |
| Year-4 |                    |                      |                   |
| Total  | 322,065     | 46,313        | 368,378    |

Has the protocol been presented amongst Division level research forum for their inputs/comments and advice/ suggestions? Whether the comments received from the research forum are addressed in the protocol?

☒ Yes ☐ No

If 'no' is the response, its reason(s) in brief:

## **List of Abbreviations**

SRHR - Sexual and reproductive health and rights

SRH - Sexual and reproductive health

FP - Family planning

DV - Domestic violence

BHDSS - Baliakandi health and demographic surveillance system

KII - Key Informant Interview

IDI - In-depth Interview

FGD – Focus group discussion

## Project Summary

[The summary, within a word limit of 300, should be stand alone and be fully understandable.]

Principal Investigator: [name] [name]

Research Protocol Title: Development and testing of Balika Bodhu: a social norm intervention to address denial of sexual and reproductive health and rights to married adolescent girls in rural Bangladesh

Proposed start date: 01/01/2023

Estimated end date: 31/03/2025

### Background (brief):

#### (i) Burden:

Sexual and reproductive health and rights (SRHR) are vital to one's health and development. Over the last few decades Bangladesh, known as a patriarchal society, has made remarkable progress in improving contraceptive use, and maternal health. However, the progress has not been consistent in different SRHR domains and is not uniform across different groups of reproductive aged females. The progress was particularly slow in realising SRH rights of the women. Evidence suggests that choice and consent of females are ignored in all spheres of SRHR and that patriarchal gender and social norms, and discriminatory laws and practices in Bangladesh perpetuate denial of SRHR to females. Due to high prevalence of child marriage in Bangladesh (59%) (NIPORT & ICF, 2019) a huge proportion of adolescent girls are married before reaching 18. In a patriarchal setting such as Bangladesh with very strong gender and age hierarchies these child brides typically command the lowest power in the marital home. They typically have lower education than those who get married in adulthood. They also lack voice and bargaining skills. In such a context, the husband or mother-in-law may figure prominently in decisions about using contraception and the timing of childbearing. In this context, denial of SRHR usually becomes part of their lived experiences.

#### (ii) Knowledge gap:

Although social norms are recognised as one of the main drivers of denial of SRHR to married adolescent girls (MAG), social norms theories and approaches to programming are relatively new and there has been little attempt to develop and rigorously test interventions to address such social norms worldwide and in Bangladesh. Also, a handful of programmes have been implemented worldwide and in Bangladesh to empower partnered female adolescents for promoting SRHR. But, we argue that conceptualization of empowerment in these initiatives were often not grounded in solid theory and evidence. Thus, empowerment programmes for women and girls often fail to include a critical component, namely, movement building and collective agency and critical consciousness, without which empowerment cannot take place in its true sense.

#### (iii) Relevance:

The current study proposes to develop and test Balika Bodhu, a social norm intervention to address the gaps in programming and in the literature combining a comprehensive empowerment programme for MAGs with engagement of other stakeholders to increase demand, access and practice of positive behaviours in relation to SRHR among these MAGs. Balika Bodhu covers married adolescent girls aged 15-19 years.

### Hypothesis (if any):

Balika Bodhu, a social norm intervention on sexual and reproductive health and rights (SRHR) combining a comprehensive empowerment package for married adolescent girls (MAGs) and positive engagement of relevant stakeholders will significantly improve demand, access and practices regarding SRHR among MAGs in family planning (FP) use, conception, and SRH service uptake.

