### Objectives:

Primary objective:

- (iv) To develop Balika Bodhu, a social norm intervention combining empowerment of MAGs and mobilisation of relevant stakeholders to promote demand for, access to, and practices of SRHR, including FP use, conception and SRH service uptake.

- (v) To measure the effect of Balika Bodhu in increasing demand for, access to, and practices of SRHR (FP use, conception, and SRH service uptake) of MAGS.

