### Specific Objectives:

Describe the specific objectives of the proposed study. State the specific parameters, gender aspects, biological functions, rates, and processes that will be assessed by specific methods.

Primary objective:

- (1) To develop Balika Bodhu, a social norm intervention combining empowerment of MAGs and mobilisation of relevant stakeholders to promote demand for, access to, and practices of SRHR, including family planning (FP) use, conception, and SRH service uptake.
- (2) To measure the effect of Balika Bodhu in increasing demand for, access to and practices of SRHR (FP use, conception, and SRH service uptake) of MAGS.

Secondary objectives:

- (3) To measure the effect of Balika Bodhu on empowerment of MAGs;
- (4) To measure the effect of Balika Bodhu on social norm regarding SRHR of MAGs;
- (5) To explore how change happens or why change does not occur.

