#### ***Survey tools***

Three separate questionnaires will be developed to interview the married adolescent girls, their husbands, and the community members. The MAGs will be asked about their socio-economic and demographic characteristics, intrinsic, instrumental and collective agency, FP, first conception, unwanted pregnancy, birth interval, intimate partner violence (IPV), etc. In each of the SRHR domains studied, we will explore adolescent girls' knowledge, attitudes and practices with a focus on communication, negotiation, consent, choice and decision-making. Husbands of the MAGs will be asked about their knowledge and attitudes regarding SRHR relevant to them and to the MAGs, while the community members will be asked about social norms regarding SRHR of MAGs. The questionnaires will be developed in English and then translated into Bengali. The Bengali version of the questionnaires will be pre-tested, piloted and finalized. The English version of the questionnaires will be updated following the final Bengali questionnaire.

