### Study outcomes and measurement of study variables

The study outcomes will be measured after the completion of the intervention implementation. The primary outcome of this study is - increase in instrumental agency of MAGs in decision making regarding SRHR (i.e., FP use; timing of first conception; and number of children to have). Table 2 presents the primary and secondary outcomes to be measured among different target groups.

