**Table 2. Different outcomes to be measured among different target groups of Balika Bodhu**

| Sl                        | Outcome                                                                                                                                  | MAGs | Husbands of MAGs | Community members |
|---------------------------|------------------------------------------------------------------------------------------------------------------------------------------|------|------------------|-------------------|
| Primary outcome    |                                                                                                                                          |      |                  |                   |
| 1                         | Instrumental agency of MAGs in decision making regarding SRHR (i.e., FP use; timing of first conception; and number of children to have) | √    |                  |                   |
| Secondary outcomes |                                                                                                                                          |      |                  |                   |
| 2                         | Intrinsic agency of MAGs                                                                                                                 | √    |                  |                   |
| 3                         | Instrumental agency of MAGs                                                                                                              | √    |                  |                   |
| 4                         | Collective agency of MAGs                                                                                                                | √    |                  |                   |
| 5                         | Critical consciousness (perceived inequality, egalitarianism and critical action) regarding gender inequality in the society             | √    |                  |                   |
| 6                         | Knowledge of MAGs regarding FP and conception                                                                                            | √    |                  |                   |
| 7                         | Positive attitudes of MAGs regarding FP and conception                                                                                   | √    |                  |                   |

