| 19                        | Positive attitudes regarding agency of MAGs regarding SRHR among the community members                                                   |      |                  | √                 |
| 20                        | Positive attitudes of community members regarding violence against women                                                                 |      |                  | √                 |
| 21                        | Positive attitudes of community members regarding gender roles within household                                                          |      |                  | √                 |
| 22                        | Positive social norms regarding SRHR of MAGs                                                                                             | √    |                  | √                 |

**Instrumental agency of MAGs in decision making regarding SRHR (i.e., FP use; timing of first conception; and number of children to have)**

The MAGs will be asked about the main decision maker regarding: (a) FP use; (b) timing of first conception; and (c) number of children to have. The response options included '1=the MAG herself', '2=husband', '3=jointly' and '4=someone else'. A follow up question, 'what kind of joint decision it was', was asked if the response was 'jointly'. The response options included '1=he voiced his choice and I agreed', 'he voiced choice and forced me to agree', and '3=I voiced my choice and he agreed'. A MAG will be considered agentic in decision making regarding a specific theme of SRHR and will be coded as 'Yes=1' if she decided herself or it was a joint decision without any force on her, and 'No=2' otherwise. We will generate a summative score, with a higher score indicating higher agency.

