### **Knowledge, attitudes, communication, negotiation and practices of MAGs regarding SRHR**

The MAGs will be asked about their knowledge, attitudes, practices, needs, consent, choice, communication and negotiation regarding FP use, conception and SRH service uptake. The questions will heavily draw upon the standard Demographic and Health Survey questionnaire (NIPORT & ICF, 2019), SAFE ([name] et al., 2018), IMAGINE and AdSEARCH FGWs Cohort questionnaires.

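### The hypothesis and objective 2 claim better practices in FP use and conception, but none of the 22 listed outcomes is contraceptive use or pregnancy

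*Protocol*

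**What the plan says.** The hypothesis (Project Summary, repeated under Hypothesis to be tested) is that the intervention "will significantly improve demand, access and practices regarding SRHR among MAGs in family planning (FP) use, conception, and SRH service uptake". The second primary objective (Specific Objectives, and likewise in the Project Summary) is "To measure the effect of Balika Bodhu in increasing demand for, access to and practices of SRHR (FP use, conception, and SRH service uptake". The section Quantitative data analyses states that the endline will assess impact on empowerment, on social norms, and on positive practices, as three separate items.

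The primary outcome is "increase in instrumental agency of MAGs in decision making regarding SRHR (i.e., FP use; timing of first conception; and number of children to have". On each of the three themes a girl counts as agentic "if she decided herself or it was a joint decision without any force on her", and the themes are summed.

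Table 2 lists 22 outcomes, of which numbers 2 to 22 are secondary. The Survey tools section says that girls will be asked about "FP, first conception, unwanted pregnancy, birth interval, intimate partner violence (IPV), etc". The section on knowledge, attitudes, communication, negotiation and practices adds: "The MAGs will be asked about their knowledge, attitudes, practices, needs, consent, choice, communication and negotiation regarding FP use, conception and SRH service uptake".

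**The concern.** A claim about practices in FP use and conception needs at least one outcome that records use or conception. Without one, every listed outcome could succeed or fail and the trial would still not say whether contraceptive use or pregnancy changed. The protocol's own background motivates the study by teenage pregnancy, short birth intervals and larger families, and the couples and community sessions cover teenage and unwanted pregnancy. None of these is an outcome. If use or pregnancy is analysed later, the definition, denominator and direction of benefit would be chosen with the data in hand.

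**Working it through.** No arithmetic decides this point. The check sets the claims beside the outcome list and the variable definitions.

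**1. Behaviours claimed.** The hypothesis and objective 2 name three: FP use, conception and SRH service uptake.

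**2. What the 22 outcomes in Table 2 measure.**

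- Decision-making agency on FP, first conception and number of children: outcome 1 (1)
- General agency scales: 2, 3, 4 (3)
- Critical consciousness: 5 (1)
- Knowledge: 6, 12, 17 (3)
- Attitudes to FP and conception: 7, 13, 18 (3)
- Who starts the couple's conversation: 8 (1)
- Attempts to negotiate: 9 (1)
- Abortion and post-abortion care, and help seeking after violence: 10 (1)
- Intimate partner violence: 11 (1)
- Attitudes to girls' agency: 14, 19 (2)
- Attitudes to violence: 15, 20 (2)
- Attitudes to household gender roles: 16, 21 (2)
- Social norms: 22 (1)

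Sum: 1+3+1+3+3+1+1+1+1+2+2+2+1 = 22. Contraceptive use: 0 of 22. Pregnancy or its timing as an event: 0 of 22. Service uptake is partly covered, by outcome 10.

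**3. Variable definitions.** From the primary outcome through to community social norms, no variable is defined for current contraceptive use, pregnancy since baseline, unwanted pregnancy or birth interval. The FP item under "Knowledge of MAGs regarding FP and conception" asks which methods the girl has heard of. Induced abortion appears only as the route into questions about care received.

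**4. Can the nearest outcomes move without behaviour?** Yes. Outcome 1 scores who decided and whether there was force, not what was decided. One of the joint responses is that the husband stated his choice and the girl agreed, which involves no force. A girl who freely agrees to use no contraception and to conceive early is agentic on two of the three themes, exactly as is a girl who freely chooses contraception and delay. Outcomes 8 and 9 likewise record a process, not its result.

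**5. Does the powered quantity fill the gap?** The sample size section uses 50% against 65%, two-sided 5% (sidedness assumed), 80% power, 22 girls per cluster and ICC 0.05:

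- individually randomised size: 170 per arm
- design effect: 1 + (22 − 1) × 0.05 = 2.05
- clusters per arm: 170 × 2.05 / 22 = 15.84, rounded up to 16, as stated

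The plan's figure reproduces, but it is for a girl's ability to achieve her own choice. That is not use or conception either, and the 50% is entered because the rate was unknown.

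**The case against.** The strongest reply is that this is a rights-based trial. Practices of SRHR would then mean exercising choice and consent, with FP and conception only as the domains. The Survey tools section puts its focus on communication, negotiation, consent, choice and decision-making. On that reading outcomes 1, 8 and 9 are the practices, and scoring a freely chosen pregnancy as agentic is intended.

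Part of this stands: agency is a legitimate primary outcome, and any pregnancy has no clear favourable direction for girls who want one. But the protocol separates the two constructs. Empowerment is a secondary objective, the measurement section says that it is measured through agency, and the analysis section lists it apart from practices. An agency score cannot also stand for practice.

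Four stronger readings are tempting, and the documents do not support them:

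- A reader might infer that the girl in step 4 earns the maximum primary score. The score also includes number of children, so that depends on who decided the third theme.
- A reader might infer that any later analysis of use or pregnancy would be wholly unannounced. The analysis section does announce impact on positive practices. What is missing is a listed outcome and a definition.
- A reader might infer that the survey already holds everything needed. The protocol names topics, and the questionnaire is not shown. Current modern method, fertility intention and pregnancy since baseline may or may not be items.
- A reader might infer about 80% power for a 15-point change in contraceptive use. The 50% and the ICC of 0.05 were assumed for another variable.

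It is also fair to say that a statistical analysis plan may hold variable derivations. The numbered outcome list and the objective, however, are fixed in this protocol, and they disagree here.

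**Conclusion.** The point holds. For two of the three practices named in the hypothesis and objective 2, the number of listed outcomes that measure the practice is zero. This does not invalidate the agency endpoint or the sample size. It limits what the trial may conclude: a positive result on outcomes 1, 8 and 9 supports a claim about decision-making, communication and negotiation, not about contraceptive use or conception. The conclusion rests on reading practices as distinct from empowerment, which the protocol's own objectives and analysis section do. The mismatch should be resolved before endline data are seen.

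**What to change.** Add to Table 2 as pre-specified secondary outcomes, after confirming the exact questionnaire items:

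- **Current modern contraceptive use** among girls not pregnant at endline, read alongside unmet need if fertility intention is asked. Pregnancy at endline may itself be affected by the intervention, so show this result next to the pregnancy figures.
- **Unwanted pregnancy since baseline**, with any pregnancy since baseline reported descriptively. State the denominator for girls already pregnant at baseline: the application form includes pregnant women, and the ethics section expects some girls to be pregnant.

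If these are not added, restrict the hypothesis and objective 2 to decision-making, communication and negotiation about FP and conception, so that no effect on use or conception is claimed.

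The first option costs protocol wording and two or three more secondary tests on top of a list of 22, all planned at p < .05. It also costs any questionnaire item found to be missing. The second costs wording only. Under either option, claim no power for use or pregnancy, since the protocol gives no rate or ICC for them.
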